**Figure 1 F1:**
[figure not shown]
Clinical timeline for the CERT-D. Participants will complete 2 training sessions per week (16 sessions total) over the 8-week intervention period.

### Inclusion and Exclusion Criteria

Individuals with mild–moderate MDD according to DSM-IV-TR criteria (17) will be recruited for the current study. Severely depressed subjects will not be included, as the complexity from treatment tasks would likely result high rates of deterrence. Subjects identified through screening with bipolar or anxiety disorders will be excluded, as will subjects with schizophrenia, a learning disorder, eating disorder or a pervasive developmental disorder. Subjects with current brain injury or impairment which could affect cognitive function (e.g., neurodevelopmental disorders, dementia) will be excluded. In addition, subjects will be withdrawn following subsequent severe brain/head injury, development of dementia, psychosis, or development of neurological conditions such as multiple sclerosis or Parkinson’s disease.

### Ethics

The CERT-D has been approved by the Human Research Ethics Committees at the Royal Adelaide Hospital (approval number: R20170611) and The University of Adelaide (approval number: R20170611). All details of participant involvement will be conveyed to study participants both in writing and verbally before informed consent is obtained.

There are no severe adverse effects expected to result from the current treatment. However, participants will be withdrawn from treatment if they demonstrate a significant increase in depression symptom severity [20% increase in Montgomery Asberg Depression Rating Scale (MADRS) score] and referred to their treating psychiatrist or GP.

### Randomization Process

After screening, subjects will be randomly allocated with computer software to receive either personalized or standard (non-personalized) treatment (see Figure 2). In both the standard and personalized intervention groups each treatment session will consist of domain-specific tasks. Every treatment session will be repeated at least once, to ensure that subjects have the opportunity to practice the treatment tasks.

**Figure 2 F2:**
[figure not shown]
CERT-D randomization process. Several streams of treatment are available for subjects in the personalized group (high cognition, high emotion, high social cognition, broad impairment), whereas treatment is the same for every participant in the standard treatment group.

### Personalized Treatment

Personalized interventions will be tailored to address subjects’ most impaired domains. Domain-specific tests will be administered at baseline to determine the modality and degree of individual impairment. On the basis of baseline deficits, subjects in the personalized group will be allocated to one of four potential treatment arms; (1) high cognition treatment, (2) high emotion treatment, (3) high social cognition treatment, and (4) broad impairment treatment (see Figure 2). Subjects will be allocated to streams 1, 2, or 3 if impairment is primarily represented in one of the three baseline domains. In treatment arms, 1–3 subjects will complete a greater number of intervention sessions devoted to the domain of primary dysfunction. Subjects who are significantly impaired in two or more domains will be allocated to broad impairment treatment. Broad impairment treatments will incorporate a similar number of intervention sessions in each domain, but will be initiated more gradually (i.e., initial treatment sessions will be shorter in duration) and will use simpler tasks.

### Standard Treatment

Subjects allocated to the standard (i.e., non-personalized) intervention will receive an identical intervention regardless of baseline impairment. The standard intervention will be comprised of approximately an equal number of treatment sessions in each domain. Unlike broad impairment treatment, standard treatment sessions will be the full duration from the outset and the difficulty curve of treatment tasks will be steeper.

## Clinical, Self-Report, and Cognitive Assessments

### Screening

Participants will be screened for presence of MDD with the MINI 600 Neuropsychiatric Diagnostic Interview. The MINI is well validated and has demonstrated high specificity and sensitivity, as well as close concordance with the American Psychiatric Association Diagnostic Criteria (SCID), and the Composite International Diagnostic Interview (ICD-10) (53, 54). The MADRS will also be administered as a measure of depression symptom severity (55).

### Assessment Visits (Baseline—6 Months Post-RCT)

In total, six assessments of functioning and performance will occur over the CERT-D timeline (see Figure 1). In the intervention period, subjects will complete assessments at baseline, 4 weeks (mid-RCT), and 8 weeks (end of RCT). The observational period will comprise assessments in week 9 (baseline post-RCT), as well as 3 and 6 months post-RCT.

#### Psychosocial Functioning

Psychosocial functioning will be assessed with the Functioning Assessment Short Test (FAST); a clinician administered 24-item scale. The FAST includes questions which gauge subjects’ abilities across several psychosocial domains of daily living (e.g., autonomy, leisure, financial issues). The FAST takes approximately 6 min to complete (9) and will be administered by a clinician blind to experimental group allocation.

#### Cognitive Functioning

Cognitive functioning will be assessed with the THINC-it tool; a digitally administered screening instrument for cognitive impairment in depression. The THINC-it involves four objective tests of cognitive performance, including choice reaction time, a *1*-back memory task, the Trail Making Test Part B and digit symbol substitution. The THINC-it also includes a 5-item component of the self-reported perceived deficit questionnaire, as an indication of retrospective cognitive dysfunction (56).

#### Emotion

Participants’ emotional state will be assessed with the Positive and Negative Affect Schedule (PANAS), which requires subjects to indicate the intensity of current and recent emotions. Scores are calculated separately for positive and negative emotions, with higher scores indicating greater intensity. The separability of positive and negative mood scores enables discriminate bilateral mood evaluation, which is not possible with unilateral scales or with measures of depression symptom severity alone. The PANAS has well-supported psychometric properties, including high internal consistency and convergent and discriminant validity (57, 58).

#### Social Cognition

The Weschler Adult Intelligence Scale Advanced Clinical Solutions Social Cognition Test (WAIS-IV-ACS) will be used to assess participants’ social cognition. This component of the WAIS was developed in response to the finding that memory for faces and affect recognition was independent of other cognitive abilities, suggesting a unique neuropsychological construct in social cognition (38). The test involves three tasks designed to identify social cognitive impairment: Affect Naming, Prosody-Face Matching, and Prosody-Pair Matching.

#### Depression Symptom Severity

Depression symptom severity will be assessed with the MADRS and the Structured Interview Guide of the Hamilton Anxiety and Depression Scale (SIGH-AD). The SIGH–AD is a 31-item structured interview that combines the Hamilton Depression Scale (HAM-D, 17 items) and the Hamilton Anxiety Scale (HAM-A, 14 items) (59).

#### Work Productivity

Two scales will be used to evaluate occupational functioning: The Endicott Work Productivity Scale (EWPS) and the Work Productivity and Impairment Questionnaire (WPAI). Both the EWPS and WPAI are self-report questionnaires designed to measure occupational productivity (60, 61). Importantly the EWPS measures overall occupational impairment, whereas the WPAI measures the extent to which a particular issue (e.g., depression) negatively affects occupational functioning.

#### Resilience

Resilience will be assessed with “The Resilience Scale” (62). The scale involves completing a 26-item Likert scale, of which each item makes a broad statement measuring the participants’ perceived resilience (e.g., “I usually manage one way or another”). The Resilience Scale has shown high internal consistency and concurrent validity (63), as well as validation with a number of age and ethnic groups (64).

#### Functional Disability

Disability in daily life will be evaluated with the Sheehan Disability Scale (65, 66). This will involve participants self-reporting the extent to which depression symptoms disrupt three domains: (1) work/school, (2) social life, and (3) family life/home responsibilities. The Sheehan disability scale achieves high internal consistency (0.89) and concurrent validity, with high scores are indicative of mental health disorders (65).

#### Cognitive Failures

Cognitive failures can be defined as everyday slips of memory and attention (e.g., forgetting a colleague’s name). The current study will evaluate cognitive failures with the Cognitive Failures Questionnaire (CFQ), which gages the frequency of cognitive failures experienced in the past 6 months. The CFQ appears to have acceptable construct validity, as factor analysis has indicated that CFQ items load primarily to a single construct (67).

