## Methods

### Objectives

The primary objective of the CERT-D is to evaluate whether treating cognition, emotion processing, and social cognition leads to immediate and longitudinal benefit in psychosocial functioning. To achieve this objective, participants will complete either a personalized or standard (non-personalized) treatment devoted to increasing performance in these domains. Participants in the personalized group will receive a tailored treatment incorporating a greater number of sessions devoted to their domain(s) of primary baseline dysfunction. By contrast, the standard treatment group will complete a pre-established battery of treatment independent of baseline deficits.

The key hypotheses and aims of the current study are as follows:
*Hypothesis 1*:Overall, psychosocial functioning will be improved at 8 weeks [end of randomized, controlled treatment (RCT)] relative to baseline. Psychosocial functioning in the observational period (post-RCT) will not decline at 3 and 6 months relative to post-RCT baseline.*Related Aim*:To evaluate which subdomains of psychosocial function (e.g., autonomy, social relationships) are sensitive to change over time from the CERT-D.*Hypothesis 2*:Performance in secondary outcome measures will improve at 8 weeks relative to baseline, and will be retained over a 6-month observational period. Secondary outcomes include occupational functioning, cognitive failures, functional disability, resilience, and depression symptom severity.*Hypothesis 3*:It is expected that the personalized treatment group will display greater psychosocial improvement at 8 weeks (compared to baseline) than subjects who complete a standard treatment.*Hypothesis 4*:Biological and genomic signatures will be associated with psychosocial functioning, as well as cognitive, emotional, and social cognitive performance.

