### Study Design and Recruitment

The CERT-D study will commence in July 2017. The study will be a RCT, comparing the clinical efficacy of a personalized and standard intervention. Psychosocial functioning is considered the primary outcome. An effect size of approximately *d* = 0.5 is expected with regards to change in psychosocial function over the intervention. Given the intended sample size of 100, the study will achieve statistical power of 89% (1 − β = 89). The rationale for this “medium” effect size is that previous interventions have found positive outcomes approximate to this magnitude (5, 35), for example in cognitive functioning.

The trial will include 16 treatment sessions designed to improve cognition, emotion processing, and social cognition administered over an 8-week period. Assessments will occur at baseline, 4 weeks (mid-RCT), 8 weeks (end of RCT), and in the observational period at baseline (week 9) and 3 and 6 months post-RCT (see Figure 1). Assessments will measure psychosocial functioning, cognition, emotional state, social cognition, as well as occupational functioning, depression symptom severity, functional disability, cognitive failures, and resilience. Three assessment visits will also include taking blood for biomarker and genetic analysis. Recruitment will include individuals between the ages of 18 and 75, who will be invited to participate *via* research clinics of the Department of Psychiatry, University of Adelaide, and within the Central Health Network in Adelaide, South Australia. It could be argued that the age range should be restricted to younger adults (<60), such that subjects with geriatric depression are excluded. However, recent work has suggested that cognitive training strategies are efficacious in the treatment of geriatric depression (47, 51, 52). Given the current intervention shares many components of traditional cognitive training, it is suggested that the CERT-D intervention should benefit older (i.e., 60–75 years) patients.

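### The Cognitive Failures Questionnaire looks back 6 months, so its 8-week change is likely to be heavily diluted and its retention comparison is confounded by the moving recall window

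*Protocol article*

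**What the plan says.** The Cognitive Failures section of the protocol article says that the trial will use the CFQ, "which gages the frequency of cognitive failures experienced in the past 6 months". It mentions no shortened or modified recall period.

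Hypothesis 2, under Objectives, reads: "Performance in secondary outcome measures will improve at 8 weeks relative to baseline, and will be retained over a 6-month observational period". The scale's construct is on the list to which this applies: "Secondary outcomes include occupational functioning, cognitive failures, functional disability, resilience, and depression symptom severity". The section on intervention outcomes and analyses repeats the expectation.

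Study Design and Recruitment states that the sessions are "administered over an 8-week period". It places assessments at baseline, weeks 4, 8 and 9, and 3 and 6 months post-RCT. The measures taken there include the main domains "as well as occupational functioning, depression symptom severity, functional disability, cognitive failures, and resilience". Nothing in the article discusses how the CFQ's recall period relates to these visits.

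**The concern.** A questionnaire that asks about a period measures that period, not the day it is filled in. When the period is much longer than the time since baseline, the follow-up answer and the baseline answer describe largely the same weeks, and a real change is mixed with time before treatment.

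Two tests in Hypothesis 2 are exposed:

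- **The 8-week change.** A true benefit would appear much smaller than it is, so a null CFQ result at the end of treatment would say little.
- **Retention.** As visits move later, pre-treatment weeks leave the window and post-treatment weeks enter. The score can improve for that reason alone, and a benefit that has faded can look preserved. This is the more serious of the two, because it can support a false conclusion. A larger sample would not remove it.

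**Working it through.** The article gives no figure for this overlap, so there is none to reproduce.

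**Inputs**
- Recall window of 6 months, taken as 26 weeks (Cognitive Failures).
- Treatment from week 0 to week 8, and the visit times (Study Design and Recruitment; Assessment Visits). Counting 13 weeks per 3 months from the end of treatment, 3 months post-RCT is week 8 + 13 = 21 and 6 months post-RCT is week 8 + 26 = 34.
- The contrasts in Hypothesis 2 (Objectives).

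**Step 1: share of the window before treatment.** At week *t* this is max(0, 26 − *t*)/26.

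| Visit | Week | Pre-treatment weeks | Share |
|---|---|---|---|
| End of RCT | 8 | 18 | 69% |
| Observational baseline | 9 | 17 | 65% |
| 3 months post-RCT | 21 | 5 | 19% |
| 6 months post-RCT | 34 | 0 | 0% |

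The result is not sensitive to how a month is counted. With 6 months as 24 weeks, the week-8 share is 16/24 = 67%. Week 4 is left out because no stated test uses it.

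**Step 2: how much of an effect registers at week 8.** Assume first that respondents weight all 26 weeks evenly.
- Immediate, full effect from week 0: 8/26 = 31%.
- Effect building linearly over the 8 weeks, so averaging half its final size: (8 × 0.5)/26 = 4/26 = 15%.

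Even weighting is an assumption; the article says nothing either way. If a fraction *w* of the respondent's attention falls on the last 8 weeks, the share of an immediate effect that registers is *w*. That runs from 31% under even weighting towards 100% if earlier weeks are ignored.

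**Step 3: what this could mean for power (illustration only).** The article gives no expected CFQ effect. Suppose a within-person standardized change of 0.5, a value the article states for psychosocial function, with n = 100, a two-sided 5% level and an unchanged standard deviation. Dilution gives 0.5 × 0.308 = 0.154 or 0.5 × 0.154 = 0.077. Power falls from 99.9% to 33% or 12%.

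**Step 4: retention.** Under even weighting and an immediate effect, the apparent effect as a share of the full one is (8 + *k* × post-treatment weeks in the window)/26 up to 3 months, where *k* is the fraction of benefit kept after week 8. At 6 months post-RCT the window contains only post-treatment weeks, so the share is *k*.

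| True course after week 8 | Week 8 | Week 9 | 3 months | 6 months |
|---|---|---|---|---|
| Fully kept (*k* = 1) | 31% | 9/26 = 35% | 21/26 = 81% | 100% |
| Half lost (*k* = 0.5) | 31% | 8.5/26 = 33% | 14.5/26 = 56% | 50% |
| Entirely lost (*k* = 0) | 31% | 8/26 = 31% | 8/26 = 31% | 0% |

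A constant benefit looks as if it keeps growing. A halved benefit looks like further improvement at both follow-ups. A benefit lost at once looks fully retained at 3 months.

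**The case against.** A reader might infer that the CFQ cannot show any change at 8 weeks. The document does not support that. Eight of the 26 weeks lie within treatment, so part of an effect can register, and people asked about 6 months may answer mainly from recent experience. The 69% describes the calendar; it is not a measured loss of sensitivity. This objection stands, which is why the conclusion is dilution of uncertain degree. Recency weighting would shrink the distortion, but by an amount the article gives no means of knowing.

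Other limits are also fair:

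- Both arms complete the same questionnaire, so dilution does not by itself favour either arm. A positive 8-week result would be conservative, and no false-positive risk at 8 weeks is shown.
- The article gives no visit-by-visit schedule for each scale, and the timeline figure is not available here. The week-8 point does not depend on it, since Hypothesis 2 names that contrast. The week-9 figure matters only if that visit serves as the reference for retention, as the post-RCT baseline does in Hypothesis 1.
- The CFQ serves one of five named secondary outcomes. The THINC-it also contains a short self-report component on perceived cognitive deficits, so self-reported cognition does not rest on the CFQ alone.

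These points limit the stakes. None reconciles a 6-month recall period with an 8-week contrast and a retention test built on overlapping windows.

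**Conclusion.** The mismatch is real and rests on the article's own text, which fixes both the recall period and the contrast; it is not a detail left to a fuller document. The calendar shares in step 1 are firm. The sizes in steps 2 and 4 depend on even weighting of the window and on the assumed time course of the effect. Under those assumptions the 8-week CFQ change shows roughly 15% to 31% of the true effect, and more if recent weeks dominate recall.

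As planned, a null 8-week CFQ result would be hard to interpret, and apparent retention or later gain could be partly or wholly a window effect. Only the 6-month post-RCT visit has a window free of pre-treatment time. The problem is confined to a secondary outcome and leaves the primary FAST analysis untouched, but it should be corrected before CFQ results are used to support Hypothesis 2.

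**What to change.** Choose one of two routes and state it in the plan.

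1. **One shorter reference period for the CFQ at every visit, including baseline.** With the past 4 weeks, for example, the week-8 window covers weeks 4 to 8, entirely within treatment, and the 3- and 6-month windows lie entirely after it. Week 9 would be dropped for this scale, because its window would share 3 of 4 weeks with that of week 8; week 8 then becomes the reference for retention. Cost: the instruction departs from the version whose validity the article cites.

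2. **Keep the 6-month version and make baseline to 6 months post-RCT the CFQ endpoint.** Remove the CFQ from the 8-week and retention tests of Hypothesis 2, or report it there only as attenuated and descriptive. That visit is already planned, so only the endpoint definition changes. Cost: the CFQ test comes later, with more time for drop-out and outside influences, and this scale has no end-of-treatment test.

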#### Blood Specimen

Blood taking will occur at baseline, week 8 (end of RCT), and at 6 months post-RCT. These samples will enable analyses of biomarker associations with psychosocial functioning, as well as the effect of the CERT-D intervention on biomarker levels. Blood serum analyses will include of evaluation of cytokine concentration (e.g., IL-8, TNF), CRP levels, and neurotransmitter activity. Samples will be stored in secure refrigerators with stringent access rights at the Adelaide Health and Medical Sciences building.

## CERT-D Intervention Details

The intervention is comprised of 16 total treatment sessions. Each session will be devoted to one of the underlying domains of psychosocial functioning targeted by the CERT-D (i.e., cognition, emotion processing, social cognition). Tasks completed within sessions will be presented in both digital and pen and paper formats. Several digital tasks will be completed with the psychology experiment building language (PEBL) software (68), which incorporates a number of freely distributed psychological tests presented in a game-like manner. Other treatment tasks will be administered in a pen and paper format.

### Cognition Treatment

Cognition treatment sessions will involve cold cognition tasks, with the expectation that subjects’ performance in these tasks will improve over time. The researcher will emphasize the value of cold cognitive skills in everyday life and discuss transfer of these skills to functional domains (e.g., psychosocial functioning). Each cognition session will focus on one of three cognitive modalities: Executive functioning, visuospatial working memory, and verbal working memory (69). Executive treatment sessions will focus on attention, inhibition, problem solving and mental updating (70). Executive tasks include Berg’s card sorting test, symbol counting, and the Stroop task (68). Visuospatial treatment sessions will focus on spatial learning, mental rotation, and spatial coordination (71), including map learning (72), figure learning, Corsi blocks (73), and matrix rotation tasks (68). Verbal treatment sessions will target verbal sequencing, reading span, and digit span (74). Verbal training will utilize immediate and delayed verbal memory tasks in the SCIP battery (75), and the reading span and digit span tests in PEBL (68).

### Emotion Processing Treatment

The aim of emotion processing sessions will be to address negative emotional biases and cognitive-emotional (i.e., “hot cognition”) impairment in depression. Training tasks will attempt to increase participants’ performance in hot cognitive tasks, in which depressed patients typically underperform (34). In addition, the subject will be encouraged to discuss any cognitive–emotional issues which arise in these training sessions, which the expectation that raising awareness and understanding may help subjects cope with and overcome emotional dysfunction (e.g., emotional avoidance, poor reappraisal) (32). Emotional treatment tasks include emotional brain storming (49), an emotional *n*-back (35), and emotion word list tasks (76). Taken together, these tasks are intended to embed emotional stimuli within traditional cognitive remediation techniques (e.g., the *n*-back task). These strategies are based on the rationale that improving cognitive management and processing of emotional material will reduce negative attentional and cognitive biases in subjects with MDD (35).

